### Statistical Analysis

Analyses will use an intention-to-treat approach, including all available measurements for all students, in the groups in which they were randomized. Baseline equivalence and attrition between groups will be examined using single-level analyses, one-way analyses of variance to examine normally distributed data, chi-square analyses to examine binominal data, and Mann-Whitney *U* tests to examine nonnormally distributed data. The baseline data of the primary outcomes will be used as covariates to ensure that any differences between groups at baseline are accounted for. To examine intervention by time interaction–effects, mixed-effects regression will be used because of the multi-level nature of the data (students nested within schools). Hypothesized intervention effects will primarily be examined using mixed-effects linear regression analyses for normally distributed data and mixed-effects logistic regression analyses for categorical data. Bonferroni adjustments will be made for multiple comparisons where appropriate. Multiple imputation and regression weighting strategies will be used to examine the impact of attrition. Sensitivity analyses will be used to assess the effect of attrition on inferences drawn from the target parameters in the statistical analyses**.**

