### Study Design

This trial is registered with the Australian New Zealand Clinical Trials Registry (trial number: ACTRN12620000753954).

To determine the effectiveness of the Mind your Mate intervention, a cluster RCT will be conducted among year 9 or year 10 students (aged approximately 14 years) at 14 independent and public secondary schools in NSW from 2020 to 2021. Cluster randomization will be used to avoid contamination of the controls by the intervention group through student communication. Schools will be randomly allocated to either the Mind your Mate intervention condition or the active control condition (health education as usual). Figure 1 summarizes the anticipated recruitment, randomization, and assessment of the participants.

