### Sample Size Calculations

This trial is powered to detect intervention by time interactions in longitudinal cluster RCTs. To allow for comparisons between the two conditions, 6 schools (with at least 60 students) in each of the 2 intervention groups were required, giving a total of 12 schools (with at least 720 students). This would achieve 80% power to detect a standardized between-group mean difference of 0.2 in outcomes at the end of the trial with three measurement occasions (*P*=.05). An effect size of 0.2, which is comparable with previous trials of anxiety, depression, and substance use prevention programs [20,21,31-34], would have substantial benefits at the population level according to economic modeling [35]. It is anticipated that the majority of students in the year group of participating schools will take part in the study, based on participation rates found in previous school-based trials conducted by the research team [36-39]. To account for school dropouts during the trial, which are expected to be approximately 10% based on similar previous school-based trials [40], this study will recruit 14 schools (with at least 840 students).

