#### Randomization

Following the school principal’s approval, randomization and stratification according to gender will be conducted by a biostatistician external to the research team using the blockrand function in R (R Core Team). The school gender mix for stratification will be coeducational, predominately male, or predominately female, and the threshold for predominately male or predominately female will be at >60%. Half of the schools (n=7) will be randomly allocated to the Mind your Mate intervention condition and half (n=7) to an active control group (health education as usual). Similar to school-based interventions of this kind, students and teachers will not be blinded to intervention allocation.

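### Baseline and attrition comparisons are planned with tests that ignore school randomisation, so their p-values are too small whenever the variable clusters by school

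*Protocol article*

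**What the plan says.** Schools are the unit of allocation. Study Design gives the reason: "Cluster randomization will be used to avoid contamination of the controls by the intervention group through student communication". Randomization gives the numbers: "Half of the schools (n=7) will be randomly allocated to the Mind your Mate intervention condition", with the other seven going to control. Sample Size Calculations plans at least 60 students per school.

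For the comparison of arms at baseline and on loss to follow-up, Statistical Analysis says: "Baseline equivalence and attrition between groups will be examined using single-level analyses". It then lists "one-way analyses of variance to examine normally distributed data, chi-square analyses to examine binominal data, and Mann-Whitney *U* tests", the last for non-normal data. For the outcomes, the same paragraph takes the opposite approach: "mixed-effects regression will be used because of the multi-level nature of the data (students nested within schools".

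That paragraph also fixes the baseline values of the primary outcomes as covariates. It assigns the question of what attrition does to the results to multiple imputation, weighting and sensitivity analyses. No ICC is given anywhere in the article, and no cluster adjustment is described for the baseline and attrition tests.

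**The concern.** The paragraph recognises that students are nested in schools, then prescribes tests for two between-arm comparisons that assume they are not. This is a stated method, not a detail left to a fuller plan. When allocation is by school, the between-arm difference carries school-to-school variation. A student-level test leaves that variation out of its standard error, so p-values come out too small.

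Several characteristics collected to check baseline equivalence are likely to vary by school. Home postcode follows school location, and the sample mixes independent and public schools, while stratification is by school gender mix only. Attrition can also cluster, because the plan allows for schools withdrawing: "To account for school dropouts during the trial, which are expected to be approximately 10" per cent.

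What is at stake is the trial report. A chance difference between schools could be published as a significant baseline imbalance or as significant differential attrition. Attrition matters more. After proper randomisation, baseline differences are chance by definition, whereas differential loss over 12 months in an unblinded school trial is a real validity question.

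**Working it through.** **The plan's own figures.** The article states no error rate for these tests, so there is none to reproduce. The design numbers they rest on do reproduce: 12 / (1 − 0.10) = 13.3, rounded up to 14 schools, and 14 × 60 = 840 students.

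**Inputs.**
- Schools per arm: 7 recruited (Randomization) or 6 as powered ("6 schools (with at least 60 students) in each of the 2 intervention groups were required").
- Students per school, m = 60 (Sample Size Calculations; stated as a minimum).
- Level: two-sided 5%. The article gives .05 for the power statement only and does not state sidedness, so this is assumed for the baseline and attrition tests.
- School ICC: not stated. Assumed range 0.005 to 0.10.

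**Formula.** The design effect is DE = 1 + (m − 1) × ICC = 1 + 59 × ICC. The single-level statistic is too large by √DE, so the true rejection rate under no difference is 2 × [1 − Φ(1.96 / √DE)].

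| ICC (assumed) | DE | 1.96/√DE | True rate of the nominal 5% test |
|---|---|---|---|
| 0.005 | 1.295 | 1.72 | 8.5% |
| 0.01 | 1.59 | 1.55 | 12.0% |
| 0.02 | 2.18 | 1.33 | 18.4% |
| 0.05 | 3.95 | 0.99 | 32.4% |
| 0.10 | 6.90 | 0.75 | 45.6% |

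**Check by simulation.** 10,000 trials per setting, 7 schools per arm, 60 students each, no true difference, same order of ICCs:
- ANOVA: 8.5, 12.2, 18.6, 33.1 and 46.0%.
- Mann-Whitney: 8.3, 11.7, 18.0, 32.2 and 45.1%.
- Chi-square (event rates 10, 20 and 50%): about 8, 12, 18 to 19, 32 and 45 to 46%.
- At ICC 0 all three return about 5%, as they should.
- A t-test on school means stays between 4.5% and 5.3% at every ICC from 0 to 0.10, with 7 or 6 schools per arm.

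**An extreme case for attrition.** Suppose one school leaves and no other student is lost: 60/420 against 0/420. The pooled proportion is 60/840 = 0.0714. Chi-square = (60/420)² / (0.0714 × 0.9286 × 2/420) = 64.6, p < 0.0001. Counted in schools it is 1 of 7 against 0 of 7, Fisher p = 1.0. This is a limiting illustration, not a forecast.

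**The case against.** The strongest reply is that nothing in the trial's main inference rests on these tests. That is correct. A reader might infer that a false positive would bring in extra covariates, trigger weighting or decide whether attrition has affected the conclusions. The article does not support this. The baseline outcome covariates are set in advance. Imputation, weighting and sensitivity analyses are planned without reference to the attrition p-value. The effect analysis uses mixed models because of the nesting.

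The second reply is that the size rests on an ICC the article does not give. That also stands. It would be too strong to say that false differences will be declared far more often than 5% whatever the variable: at ICC 0.005 the rate is 8.5%. The calculation also ignores stratification by school gender mix, which would lower the rate for variables tied to that mix. In the other direction, schools larger than the 60 minimum would raise it. The direction, for any positive ICC, is not in doubt.

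The third reply concerns the whole-school example. A reader might take the allowance for school dropout to mean that attrition is expected only as whole schools leaving. The article does not say so, and Assessment Occasions plans to contact individual absent students. Nor would losing 60 of 420 students from one arm be spurious: it is a real imbalance in the data that readers need to see. The Fisher p-value of 1.0 also reflects a test with almost no power. The example shows only that a student-level p-value can present one school's decision as overwhelming evidence of an arm effect on retention.

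**Conclusion.** The point holds in limited form. The plan specifies tests that do not match its unit of randomisation, and their p-values are too small for any positive school ICC. At 60 students per school the true error rate of a nominal 5% test runs from about 8.5% to 46% over assumed ICCs of 0.005 to 0.10. It is more than double the nominal level from about 0.01 upwards. These figures assume equal schools of 60, two-sided testing at 5% and no benefit from stratification.

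The damage is confined to how baseline comparability and attrition are reported. Nothing in the article shows that the treatment-effect estimates, their tests or the planned adjustments are affected.

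**What to change.** In Statistical Analysis, replace the single-level comparisons with ones that respect school clustering.

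- **Attrition:** compare school-level proportions lost, by a t-test or by a permutation test stratified by school gender mix. Alternatively, fit a logistic model with a school random effect to within-school losses only. Report whole-school losses separately, as counts of schools per arm with the students involved. They should stay out of the random-effect model, which is poorly estimated when one school loses everyone.
- **Baseline:** give summaries by arm with standardised differences. Dropping tests is a separate reporting choice that the clustering problem does not force; if tests are kept, use cluster-adjusted ones.

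The cost is analysis wording only, with no new data or schools. The downside is lower power to detect differential attrition: a comparison of 14 school proportions has 14 − 2 = 12 degrees of freedom. A non-significant result should therefore not be read as showing equal retention, and the loss in each school should be shown alongside it.

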### Measures

#### Overview

Demographic data, including age, sex, gender, home postcode, and country of birth, will be obtained to determine the baseline equivalence of the groups. To assess academic performance, students will nominate the range that their grades usually fall into (ie, <49%, 50%-59%, 60%-69%, 70%-79%, 80%-89%, and 90%-100%). Truancy will be measured by students reporting the number of days that they had off from school in the previous year without their parents’ permission.

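### Schools are randomised within strata of gender mix, but the adjustment variables the article names for its primary models leave that stratum out

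*Protocol article*

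**What the plan says.** **Allocation** (Methods, Randomization). Schools are randomised 7 and 7, stratified in three levels: "The school gender mix for stratification will be coeducational, predominately male, or predominately female". Predominance is set at more than 60%.

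**Model** (Methods, Statistical Analysis). The target is the intervention-by-time interaction, and "mixed-effects regression will be used because of the multi-level nature of the data (students nested within schools"). Models are linear or logistic according to the outcome. The section makes the baseline data of the primary outcomes covariates. It gives no list of random terms, no estimation method and no reference distribution or degrees of freedom.

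**Other adjustment** (Fidelity and Implementation Log). A logbook completed by one teacher per school at 12 months is to be used to control for other well-being programmes.

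**Demographics** (Measures, Overview). "Demographic data, including age, sex, gender, home postcode, and country of birth, will be obtained to determine the baseline equivalence of the groups". They are not named as model covariates.

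**Size** (Sample Size Calculations). "This trial is powered to detect intervention by time interactions in longitudinal cluster RCTs". The requirement is "6 schools (with at least 60 students) in each of the 2 intervention groups were required", which makes 12 schools and 720 students in all. The section says this gives "80% power to detect a standardized between-group mean difference of 0.2 in outcomes at the end of the trial with three measurement occasions". Recruitment is raised to 14 schools to allow for school dropout.

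**The concern.** An analysis should reflect the way units were allocated. Stratifying by gender mix forces the arms to be similar on that factor, so the true sampling variance of the group difference no longer contains the between-stratum part. A model without the stratum still counts that part as unexplained variation between schools. The estimate keeps its precision, but the reported standard error does not show it. Intervals are then too wide and tests conservative.

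This matters because the trial is sized for a 0.2 SD difference on 12 schools. Gender mix was considered important enough to stratify on, and there is little precision to spare.

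A second, conditional matter arises from the same small number of schools. Once the stratum is in the model, the method of inference (z, or t with few degrees of freedom) has more influence on the error rate.

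**Working it through.** **1. The plan's own figures.** Without clustering, a single final comparison of 360 with 360 has SE = √(2/360) = 0.0745. Then 0.2/0.0745 = 2.683, and power = Φ(2.683 − 1.96) = 76.5% (two-sided 5%, assumed). With baseline adjustment, 80% is reached at an ICC of about 0.0038, 0.0073 or 0.0135 for a baseline correlation of 0.5, 0.6 or 0.7. The article gives neither quantity, so 80% can be neither confirmed nor refuted. The school inflation reproduces: 12/0.9 = 13.3, and recruiting equal arms gives 14.

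**2. True standard error under stratification.** Inputs from the article: 6 schools per arm, 60 students each. Assumed: total variance 1, ICC 0.02, stratum explaining 60% of between-school variance, balance within strata.

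- Between-school variance left after the stratum: 0.02 × 0.4 = 0.008
- Student part of a school mean: 0.98/60 = 0.01633
- True SE = √[(2/6)(0.008 + 0.01633)] = √0.00811 = **0.090**
- If all school variance is treated as noise: √[(2/6)(0.02 + 0.01633)] = √0.01211 = 0.110

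Simulation (random-intercept model, REML) gives a mean reported SE of **0.112** without the stratum, slightly above 0.110 because balance within strata pushes the stratum variation into the within-arm spread. The ratio is 0.112/0.090 = 1.24. With the stratum in the model, the mean SE is 0.091 against a true 0.090.

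**3. Other assumed settings** (simulated, stratum omitted).

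| Schools | ICC | Stratum share | Mean SE | True SE | Ratio |
|---|---|---|---|---|---|
| 12 | 0.05 | 0% | 0.145 | 0.148 | 0.97 |
| 12 | 0.05 | 30% | 0.148 | 0.130 | 1.14 |
| 12 | 0.05 | 60% | 0.152 | 0.109 | 1.40 |
| 14 | 0.02 | 30% | 0.102 | 0.093 | 1.09 |
| 14 | 0.02 | 60% | 0.103 | 0.084 | 1.23 |

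Type I error at nominal 5% with t inference (12 schools, ICC 0.05) is 5.0%, 2.6% and 0.8% at shares of 0%, 30% and 60% without the stratum. With the stratum it is 5.0%, 4.7% and 4.2%.

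**4. Price of the two terms.** Critical t goes from 2.228 (10 df) to 2.306 (8 df) with 12 schools, and from 2.179 (12 df) to 2.228 (10 df) with 14. If the stratum predicts nothing, intervals widen by 2.306/2.228 = 1.035 or 2.228/2.179 = 1.023.

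**5. Conditional: z inference.** If 1.96 were used in place of t, nominal 5% becomes 2[1 − T₁₀(1.96)] = 7.8% with 12 schools and 2[1 − T₁₂(1.96)] = 7.4% with 14. Simulated REML with z and no stratum effect gives 4.4% to 8.0% (12 schools) and 4.3% to 7.3% (14 schools) as the ICC runs from 0.001 to 0.05. It is near nominal at the smallest ICCs. Under z, adding the stratum removes an accidental offset: at 12 schools, ICC 0.05 and share 60%, the rate goes from 1.6% without it to 7.8% with it.

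**6. Conditional: school-by-time variation.** If baseline is an outcome occasion and the only school term is an intercept, that intercept cancels from the change contrast. The ignored design effect is 1 + 59 × ICC of change. At ICC 0.01 it is 1.59, and P(|Z| > 1.96/√1.59) = 12%. At 0.02 it is 2.18, giving 18%. If baseline is a covariate instead, simulation with a school intercept only (14 schools, assumed correlation 0.6) gives 7.0% to 7.9% with z and 4.6% to 5.3% with t on 12 df.

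**The case against.** The strongest reply is that this is a condensed article. Its covariate sentence is not worded as exclusive, and an analysis plan that is not shown may include the stratum. Leaving it out also errs on the safe side in a linear model and costs nothing if gender mix is unrelated to outcome. All of that is fair and keeps the point modest. It does not remove it. The article does say what it will adjust for, in two places, and one of those is a school-level variable recorded at 12 months. The factor that governed allocation is absent from both.

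Stronger readings are tempting. A reader might infer that the models use large-sample z inference and so give intervals that are too narrow, or that the interaction is tested as if students had been randomised individually, with rejection rates of 12% or more. The article supports neither. The phrase about nesting explains why mixed models are used and does not list the random terms. Nothing is said about z, estimation method or degrees of freedom, which an article may leave to the full plan. The 12% and 18% also need baseline to remain in the outcome vector, whereas Statistical Analysis makes it a covariate. Moreover, an omitted stratum widens intervals, so it cannot be a reason for narrow ones.

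Nor does mirroring the randomisation call for student sex in the model. Stratification was on the school's mix, so adjusting for individual sex is optional.

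**Conclusion.** The point stands in a limited form. The named adjustment set does not match the stated stratification. Following it would understate the trial's precision to the extent that gender mix predicts the tested contrast. The excess in reported standard error ranges from none at a share of 0%, through about 9% to 14% at 30%, to about 23% to 40% at 60%. These figures hold for linear models and rest on assumed ICCs (0.02 and 0.05), assumed shares and balance within strata, none of which the article gives. No figure is offered for the logistic models.

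The small-sample and school-by-time matters are requests for confirmation. The documents do not show that either fault is present.

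**What to change.** State in Statistical Analysis that school gender mix (three levels) is a fixed effect in every primary model. If baseline is kept as an outcome occasion, the stratum should also interact with time, since a constant stratum effect cancels from a change contrast just as a school intercept does.

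In the same sentence, state small-sample degrees of freedom for the linear models, such as Kenward-Roger or Satterthwaite, and say how few schools will be handled in the logistic models. Say whether baseline is a covariate or an occasion; if it is an occasion, include a school-by-time random effect.

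The cost is a change of wording and up to two school-level degrees of freedom: intervals at most about 3.5% wider with 12 schools, or 2.3% with 14, if gender mix turns out not to matter. No new data are needed, because each school's gender mix must be known in order to randomise it.

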**Methods:**

Participants will consist of approximately 840 year 9 or year 10 students (60 students per grade per school) from 14 New South Wales high schools in Sydney, Australia. Schools will be recruited from a random selection of independent and public schools across the New South Wales Greater Sydney Area by using publicly available contact details. The intervention will consist of 1 introductory classroom lesson and a downloadable mobile app that will be available for use for 12 months. Schools will be randomly allocated to receive either the mHealth peer intervention or a waitlist control (health education as usual). All students will be given web-based self-assessments at baseline and at 6- and 12-month follow-ups. The primary outcomes of the trial will be the self-reported use of alcohol and drugs, anxiety and depression symptoms, knowledge about mental health and substance use, motives for not drinking, and willingness to seek help. Secondary outcomes will include positive well-being, the quality of life, and the impact of the COVID-19 pandemic. Analyses will be conducted using mixed-effects linear regression analyses for normally distributed data and mixed-effects logistic regression analyses for categorical data.

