### Aims, Objectives, and Hypotheses

This study aims to evaluate the effectiveness of Mind your Mate program among adolescents through a cluster randomized controlled trial (RCT) conducted in partnership with secondary schools. We hypothesized that the Mind your Mate intervention will be more effective than the active control group (health education as usual) in (1) delaying the uptake of alcohol and other drugs; (2) reducing anxiety and depression symptoms; (3) increasing knowledge about mental health, alcohol and other drugs; and (4) increasing help-seeking behavior.

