##### Mental Health Measures

Psychological distress in the past month will be assessed using the Kessler 6 scale [48]. Depression and anxiety symptoms during the past 2 weeks will be measured using the Patient Health Questionnaire 8 [49] and the Generalized Anxiety Disorder 7-item scale [50], respectively.

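### The 80% power is stated at P=.05 with no division of alpha; if the planned Bonferroni adjustment runs across the primary outcomes, power per test is about 62% for four tests and 59% for five

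*Protocol article*

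**What the plan says.** Sample Size Calculations gives one power statement for the whole trial: "This would achieve 80% power to detect a standardized between-group mean difference of 0.2 in outcomes at the end of the trial". The significance level attached to it is 0.05, and each student is measured three times. The statement rests on 6 schools of at least 60 students per arm, so 12 schools and 720 students. Recruitment is raised to 14 schools to cover an expected school dropout of about 10%. The section mentions neither a division of alpha nor a lead outcome.

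The Abstract (Methods) names five primary areas. Alcohol and drug use comes first, followed by "anxiety and depression symptoms, knowledge about mental health and substance use, motives for not drinking, and willingness to seek help". Aims, Objectives, and Hypotheses has four numbered hypotheses: substance use uptake, anxiety and depression symptoms, knowledge, and help seeking. The Primary Measures section places many instruments and items at the same level, with none ranked above another.

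Statistical Analysis then states: "Bonferroni adjustments will be made for multiple comparisons where appropriate". It gives no family and no divisor.

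**The concern.** A Bonferroni adjustment over m tests uses 0.05/m for each test, while the power figure was set at 0.05. With two or more primary tests in the family, the sizing and the analysis work at different significance levels. A reader who takes the 80% as the chance of detecting a difference of 0.2 on a primary outcome would then be misled, and a null result would be read as stronger evidence than it is.

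If the adjustment is judged unnecessary across primary outcomes, the two sections agree at 0.05. The trial then has several unranked primary outcomes, each tested at 5%, and the chance of at least one false-positive primary result exceeds 5%. On neither reading does the article deliver both 80% power per test and 5% familywise error.

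The divisor cannot be read off the article, because its lists do not line up fully. Motives for not drinking is primary in the Abstract and under Primary Measures but belongs to no hypothesis. Under Mental Health Measures, "Psychological distress in the past month will be assessed using the Kessler 6 scale", yet distress is in neither the Abstract's primary list nor the hypotheses.

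**Working it through.** **Inputs from the article.** Power 80%; significance level 0.05 (sidedness not stated, two-sided assumed); standardized difference 0.2; 6 schools × 60 students = 360 per arm; three occasions; school dropout about 10%; four hypotheses; five primary areas in the Abstract.

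**Not in the article.** The intraclass correlation and the correlation between occasions.

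**Step 1: the plan's own figures.** The school inflation reproduces: 12/0.9 = 13.3, rounded up to 14. The 80% cannot be strictly checked without the missing correlations. Ignoring clustering, a two-sided end-of-trial comparison of 360 with 360 gives 76.5%. A three-occasion slope contrast with SD √(2(1−ρ)), ρ = 0.55 and no school-level slope variance gives 80.7%. So 80% at 0.05 is attainable under favourable assumptions, and it is taken as given below.

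**Step 2: power at the adjusted level.** Power of 80% at two-sided 0.05 implies a noncentrality of 1.960 + 0.842 = 2.802. For m tests:

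power = Φ(2.802 − z(1 − 0.05/(2m)))

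For m = 4 the critical value at 0.0125 is 2.498, so power = Φ(0.304) = 0.619. The t column repeats this with a noncentral t on 10 df (12 schools − 2), calibrated to 80% at 0.05. The 14-school column multiplies the noncentrality by √(14/12), for the case in which no school drops out.

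| m | alpha per test | power, normal | power, t on 10 df | power, normal, 14 schools |
|---|---|---|---|---|
| 1 | 0.05 | 80% | 80% | 86% |
| 2 | 0.025 | 71% | 68% | 78% |
| 4 (hypotheses) | 0.0125 | 62% | 55% | 70% |
| 5 (Abstract areas) | 0.01 | 59% | 51% | 67% |
| 16 (upper count) | 0.003125 | 44% | 31% | 53% |

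**Where 16 comes from.** It is a reviewer's count of the content under Primary Measures, not a figure in the article: 2 knowledge + 5 alcohol (including motives) + 3 other drugs (ever use counted once) + 3 mental health + 3 help seeking = 16.

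**Step 3: the detectable effect.** The effect with 80% power scales as 0.2 × (z(1 − 0.05/(2m)) + 0.842)/2.802. This gives about 0.24 for m = 4 (0.2 × 3.340/2.802 = 0.238), 0.24 for m = 5 and 0.27 for m = 16.

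**Step 4: no adjustment.** For independent tests, familywise error = 1 − 0.95^m. This is 1 − 0.95^4 = 0.185 for four tests and 1 − 0.95^5 = 0.226 for five. Positive correlation between outcomes lowers these values.

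**The case against.** The strongest reply is that the adjustment is conditional. The article says it will be made where appropriate, and does not say that it runs across primary outcomes rather than, say, across the two follow-ups within one outcome. The 80% is expressly tied to P=.05. An article also commonly leaves the definition of a multiplicity family to the statistical analysis plan, which is not shown.

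Most of this stands, and it rules out three stronger readings that a reader might infer.

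- **That the 80% is false.** It is not shown to be wrong for a single test at 0.05. It is only not the power of a Bonferroni-adjusted test.
- **That the plan commits to about 16 primary tests.** The article gives no such number. Items such as friends' drinking or the likelihood of future drug use are described as questions asked, although they sit under Primary Measures. The families with better support are the four hypotheses and the five areas in the Abstract.
- **That the family can be chosen after the data are seen.** An analysis plan may already fix it, and the article cannot show otherwise.

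The reply does not remove the mismatch. An analysis plan can name the family, but it cannot make a power figure set at 0.05 apply to a test at 0.0125. Nor do the 14 recruited schools close the gap: even with every school retained, power is 78% for two tests and 70% for four.

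**Conclusion.** The point holds in conditional form. If Bonferroni is applied across two or more primary outcomes, the stated 80% overstates the power per test: about 71% for two tests, 62% for four and 59% for five, or 68%, 55% and 51% with a t reference on 10 df. The figures of 44% (normal) and 31% (t) for 16 tests are a lower extreme that depends on testing every counted measure separately; they should not be quoted as the plan's power. If Bonferroni is not applied, power at 0.05 is as stated, but familywise error is about 19% for four independent tests.

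All power figures assume that the 80% at two-sided 0.05 is correct for a standardized mean difference of 0.2, which cannot be verified without the intraclass and between-occasion correlations. They do not carry over to binary uptake of alcohol or drugs, which the article itself says may be uncommon at this age.

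**What to change.** Before follow-up data are analysed:

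1. Fix the confirmatory primary family in line with the four hypotheses. The investigators should choose the outcomes, bearing in mind that hypothesis 2 names both anxiety and depression and that hypotheses 1 and 3 each cover more than alcohol or mental health alone. If a hypothesis needs two outcomes, count both. Treat the remaining measures as secondary.
2. Replace the conditional Bonferroni sentence with Holm at familywise 0.05 over that family. Holm gives the same familywise control and is never less powerful than Bonferroni.
3. Restate the power, or the detectable effect, at the adjusted alpha, together with the intraclass and between-occasion correlations used. For four tests, 0.0125 gives about 62% or lower for a difference of 0.2, or a detectable effect of about 0.24 at 80% power (normal approximation).

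The cost is a change of wording in the protocol and the registration, a less favourable power statement, and the move of some measures from primary to secondary. Baseline assessment was already under way when the article was submitted, so that move should be recorded as a dated change. No extra schools or measurements are needed.
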